Insertion of a tunnelated peritoneal catheter has been shown to be an effective and safe treatment for malignant ascites.^51^ The catheter (PleurX) allows intermittent fluid drainage at home using vacuum containers. Potential benefits include the ability to improve the control of symptoms and reduce the need for large-volume paracentesis. A study including 38 patients with malignant ascites found that two patients (5%) developed peritonitis after insertion of the catheter. The study did not include a control group. A review from the National Institute for Health Care and Excellence (NICE) found eight observational studies reporting complications to the PleurX.^51^ Six studies were case series. The number of catheters requiring removal ranged from 0% to 7.5% and the total number of complications ranged from 0% to 59%. Reasons for removal of the device included infection, leakage of ascitic fluid, and loculated ascites. Ten of 172 patients (6%) developed peritonitis. The infections required removal of the catheter in two patients. Eight patients were treated successfully with antibiotics. Other complications included ascitic fluid leakage and occlusions. Only one study compared complications associated with the PleurX catheter and large volume paracentesis.^52^ The study used a retrospective design and the maximum duration of follow up was 41 months. One patient treated with the PleurX catheter developed peritonitis. The overall complication rate in the two comparison groups was 7.5%. There are no controlled studies evaluating the PleurX for non-malignant ascites. A retrospective study evaluated the risk of peritonitis following insertion of a PleurX catheter for diuretic resistant ascites in cirrhosis.^53^ The study included 149 patients and data from 200 catheter placements. Each placement is considered a separate event. Accordingly, some patients are included in the analysis more than once. In total, peritonitis was diagnosed after 19 placements (10%). Most were culture-negative. There are no data regarding the potential beneficial effects of the intervention or the use of antibiotics, but the authors report that they found no predictors of infection or mortality. The study does not include a control group.

Rationale

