Furthermore the listed parameters below occur regularly amongst patients with decompensated cirrhosis and ascites. They are thoroughly evaluated and afterwards categorized, by specialized hepatologists, as not being associated with carrying a permanent tunnelated peritoneal catheter. As a result this list of events will not be categorised at SAE but will be registered as AE:

- Hospitalisation du to large volume paracenthesis
- Alterations in type and dose of medicine
- Planned outpatient control visits due to other chronical diseases
- Hospitalisations due to chronic liver failure
- Hospitalisations due to alcohol intoxication
- Diagnosis of Hepatocellular carcinoma or other malignant diseases

Some side effects of ascites are obtained by letting the study participants answer the Quality of Life Questionnaire at every visit. Therefore these side effects will not also be listed as Adverse Events:

- Stomach pain or soreness
- Nausea
- Anorexia
- Reduced appetite
- Alterations in bowel habits
- Fatigue
- Dyspnoea
- Negative alterations in physical capability
- Leg pain

The type, potential relationship, severity, starts and end date for all AE must be recorded. The severity of the adverse event and the relationship with the study medical device must be assessed in accordance with the guidelines described below.

*The investigator must assess the relationship between an adverse event and the study medical device using the following guidelines:*

Adverse Device Effect (ADE): an adverse event related to the use of the medical device

Serious Adverse Event (SAE / pre-event): an event that results in i) death; ii) life-threatening injury or illness; iii) lasting harm to the body or bodily functions; iv) hospitalization or prolongation of existing hospitalization or required medical or surgical treatment are necessary to prevent i to iv.

Serious Adverse Device Effect (SADE): a serious incident which is related to the use of the medical device.

An almost-event is an equipment incident which does not have a serious output because of intervention before the event has evolved.

Serious incidents and near-incidents caused by improper treatment or error due to technical errors or defects in the equipment, instructions, labelling, use or maintenance of the equipment.

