The primary outcome measure is paracentesis free survival. With an estimated probability of paracentesis free survival set to 0.3 at the end of the trial, an allocation ratio of 1:1, alpha 5% and power 80%, the required sample size is estimated to be a total of 28 patients (14 patients in each group). After taking into account the risk of participant dropout the sample size is set to be 32 patients (16 patients in each group).

Statistical analyses

We plan to include all patients randomised (intention to treat) regardless of compliance or follow up. Patient characteristics will be summarised using medians with interquartile range or proportions. Groups will be compared using t-tests or chi-square tests as appropriate. The level of significance will be set to 5%. The primary outcome measure will be evaluated using Kaplan Meier Plots and log-rank tests. Univariate and multivariate logistic regression analysis will be conducted to identify potential predictors of paracentesis free survival.

Handling of data

Data will be retrieved from medical records, information provided by the patients at trial visits as well as laboratory (biochemistry) assessments and investigational results. Data will be collected to Case report forms and entered into an electronic database by the principal investigator. Case report forms from the supporting sites will be sent by secure mail to the principal investigator. The database is anonymous. A trial participant identification list will be stored safely by the principal investigator.

Missing data

During the trial, we plan to search for information about missing data in the medical records. Investigators will pursue the options of repeating biochemistry and blood analyses when this is possible. Invasive procedures will not be repeated, should data be missing after the participant has completed the trial investigations.

Quality Control

The study personnel will be trained and tested in all study related procedures to ensure adequate quality control. In particular, investigators will be tested 0to ensure the optimal use of the interventions assessed (PleurX and large volume paracentesis). All investigators are specialised hepatologists with extensive experience in the management and observation of patients with refractory ascites including experience in the use of the PleurX and large volume paracentesis through their clinical work.

Data registration and rules for the control of investigation procedures

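### The rule that an admission for large volume paracentesis is never an SAE has no arm limit, so a PleurX-arm admission caused by a catheter problem cannot be classed or reported as a SADE

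*Protocol*

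**What the plan says.** All of the classification rules are in the protocol's Adverse Events section.

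- **The list and its basis.** Certain events common in decompensated cirrhosis are "categorized, by specialized hepatologists, as not being associated with carrying a permanent tunnelated peritoneal catheter".
- **Its consequence.** "As a result this list of events will not be categorised at SAE but will be registered as AE".
- **The item at issue.** The first entry is "Hospitalisation du to large volume paracenthesis". It names no arm and makes no exception for a catheter that is blocked, leaking or out of use.
- **Seriousness.** The fourth limb of the SAE definition reads "hospitalization or prolongation of existing hospitalization or required medical or surgical treatment are necessary to prevent i to iv".
- **SADE.** This is defined as "a serious incident which is related to the use of the medical device".
- **Recording.** "The type, potential relationship, severity, starts and end date for all AE must be recorded". The investigator must also assess each adverse event's relationship to the device.

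The section on reporting of AEs and SAEs/SADEs attaches duties to SADE status. The investigator reports to the sponsor immediately and to the ethics committee annually. Fatal or life-threatening SADEs go to the authorities within 7 days and all others within 15 days.

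The Background describes the catheter as a way to reduce the need for large volume paracentesis. It gives infection, leakage and loculated ascites as reasons for removing the device, and adds: "Other complications included ascitic fluid leakage and occlusions". Under Sample Size Considerations, "The primary outcome measure is paracentesis free survival".

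**The concern.** The same event has a different meaning in each arm. For a control patient, admission for large volume paracentesis is the treatment to which the patient was randomised, and keeping it out of the SAE count is sensible. For a PleurX patient it is treatment that the catheter was meant to make less necessary, and one possible reason for it is that the catheter is not draining. The list settles the question of device relation in advance for both arms, and its stated reason concerns people who carry the catheter. It therefore cannot be read as a control-arm rule.

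The stake is the safety record of the device under test. Evaluating harms is part of the trial's objective, and adverse events, as defined in this section, are a secondary outcome. A device problem that comes to light as an admission for paracentesis would be missing from the SADE count and would not trigger the SADE reports to the sponsor, the authorities and the ethics committee.

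**Working it through.** The defect is in the text, and no stated figure needs to be reproduced. The check follows one case through the rules: a PleurX patient whose catheter is occluded is admitted and has a large volume paracentesis.

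| Question | General definitions | Exclusion list |
|---|---|---|
| Serious? | Yes: hospitalisation, fourth SAE limb | No: AE only |
| Related to the device? | Yes: occlusion is a complication named in the Background | Presumed not |
| SADE? | Yes: serious and related | No: neither element is available |
| SADE reporting? | Yes | No |

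The fourth SAE limb is awkwardly worded, but the reading used here is the one the list itself needs. Taking hospitalisations off the SAE count has a purpose only if they would otherwise be on it.

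**What is kept.** The admission is registered as an AE. Because relationship is recorded for every AE, an adverse device effect (ADE) entry remains possible. The paracentesis also counts in paracentesis free survival and in the cumulative number of paracenteses, which is collected at Visits 3 to 8.

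**What is lost.** SAE and SADE status, and the reporting that depends on it. An ADE that is barred from being serious cannot become a SADE.

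**Scale.** The protocol gives no rate of catheter problems leading to admission for paracentesis in cirrhosis. What can be shown is how sensitive an arm of this size is.

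- PleurX arm: 16 patients (Sample Size Considerations).
- One event: 1/16 = 6.25%. Two events: 2/16 = 12.5%.
- For comparison, the Potential Risks section puts the combined risk of the listed complications at 10% in each group: 0.10 × 16 = 1.6 patients.

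For an assumed probability r of such an admission per patient, the expected number is 16r and the chance of at least one is 1 − (1 − r)^16:

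| Assumed r | Expected patients | Chance of at least one |
|---|---|---|
| 0% | 0 | 0 |
| 5% | 0.8 | 0.56 |
| 7.5% | 1.2 | 0.71 |
| 20% | 3.2 | 0.97 |

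The 7.5% is the top of the catheter-removal range of 0% to 7.5% in the Background. That range comes from observational studies cited for malignant ascites, and it counts removals, not admissions for paracentesis. It serves here only as a reference value. None of the rows is an estimate for this trial.

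**The case against.** The best defence is that little is hidden. The admission is recorded, its relationship is assessed, and it counts against the catheter in the primary outcome. The reporting section also requires immediate notice of any situation that may affect participants' safety. All of this is true and it limits the point. It does not restore SAE or SADE status, which is what the SADE count and its reporting deadlines depend on.

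A second defence is that the protocol says the events are evaluated before being categorised, which could mean case-by-case review. The sentence that follows applies the outcome to the whole list, so the text operates as a blanket rule. At best it is ambiguous.

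Several stronger readings are tempting, and the protocol does not support them.

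- *A reader might infer that a PleurX-arm admission for paracentesis usually means catheter failure.* The protocol gives no reasons or frequencies for such admissions. Voluntary removal of the catheter is one alternative, and fluid accumulating faster than home drainage controls it is another.
- *A reader might infer that device failures in general drop out of the safety data.* Admissions for peritonitis, bleeding, perforation or catheter removal are not on the list and can still be SADEs. The Interventions section defines large volume paracentesis as removal of more than five litres, so admission for a smaller tap is not exempt on that definition.
- *A reader might infer a biased comparison between arms.* SADE applies only to the device, so there is no control-arm SADE count to compare.
- *A reader might size the problem from the 0.3 in the sample size, as 0.7 × 16 = 11.2 patients.* The protocol does not assign 0.3 to an arm, and the outcome includes death.
- *A reader might see a contradiction in counting the event as an efficacy failure but not as an SAE.* An endpoint event need not be a serious adverse event. The fault is only that device relation and seriousness are decided beforehand.

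**Conclusion.** The point holds in this limited form. Within one section, the exclusion list and the SAE/SADE definitions classify the same PleurX-arm admission in opposite ways, and the list prevails. If followed as written, an admission for large volume paracentesis caused by a catheter problem cannot be counted or reported as a SADE. This is a stated rule that gives a wrong classification, not a detail left to a later document.

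The number of patients affected is unknown and may be none. The effect is on SAE/SADE classification and the reporting tied to it, not on AE registration or the efficacy outcomes. It still merits correction: in an arm of 16, one or two events would shift the SADE summary by about 6 to 12 percentage points. The conclusion assumes that hospitalisation is a seriousness criterion in its own right and that the list is applied as a blanket rule. It does not depend on any assumed failure rate.

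**What to change.** Reconcile the list with the SAE and SADE definitions in the Adverse Events section:

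1. Limit the item to hospitalisation for the allocated large volume paracentesis in the control arm.
2. Add that each PleurX-arm admission for paracentesis is assessed individually for relation to the catheter (for example occlusion, leakage or loculation) and for seriousness under the section's own definitions, and is classed as a SADE when both are met.

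This takes a sentence or two in the protocol and the matching adverse event guidance. It changes classification and reporting only, not patient management. The cost is a few more SADE reports and possibly a less favourable SADE figure for the device.

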Once the catheter is placed, drainage of ascites can be done using vacuum bottles connected to the catheter (see Appendix F). A home nurse will be trained in the drainage procedure and patient monitoring by specialised company staff from Vingmed. (http://www.carefusion.com/our-products/interventional-specialties/drainage/about-the-pleurx-drainage-system/patient-information-pleurx-system/how-to-drain-at-home). The home nurse will ensure that only a maximum of two litres of ascites fluid is removed at a time.

*Large volume paracentesis*: Removal of more than five litres of ascites is defined as large volume paracentesis. Initially, an abdominal ultrasound is performed. This allows an estimate of the ascites volume and distance from the skin to the ascitic fluid. The procedure is performed with the patient lying on his back in a slightly recumbent position toward the site of paracentesis. The ultrasound is used to ensure adequate insertion of the needle in the ascitic fluid. Generally, the insertion site is inferior to umbilicus 2-3 fingerbreadths below the umbilicus. The area is cleaned with betadine in and sterile drapes applied. Using sterile technique, local anesthesia is applied to the area from the skin to the peritoneum. A small incision is made (about 1.5 cm). Subsequently, the catheter, which contains a needle is inserted. Once fluid is aspirated, the needle is removed from the plastic catheter. The catheter is then attached to the catheter bag. After the procedure, the patient remains in hospital for observation until the fluid is drained. Vital signs are checked and the amount of fluid drained is registered. After removal of 4 liters, 25 cc of albumin (25% solution) is given for every following 3 liters of ascitic fluid removed.

Potential Risks

Risks associated with peritoneal catheter and large volume paracentesis

The risks associated with insertion of a peritoneal catheter and large volume paracentesis include pain at insertion of the drain, ascites leakage, haemorrhage, hypotention, electrolyte depletion, protein depletion, peritonitis, and bowel perforation. Based on previous evidence,^51 53^ the combined risk of these adverse events is 10% in both intervention groups.

*Pain*: Infiltration of the puncture site with a local analgesic will be used before insertion of the peritoneal catheter and large volume paracentesis. The administration of local anaesthetic may be pain free or be associated with a sharp sudden pain.

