*Haemorrhage*: Less than 10% develop a local haematoma at the puncture site. More severe bleeding including peritoneal haemorrhage is described in the literature, but is very rare occurring in less than one percent.

*Hypotention, electrolyte and protein depletion*: The main risk associated with removal of ascites is hypotention, electrolyte and protein depletion. The risks occur after removal of at least four litres of fluid. Administration of albumin reduces the risk of these complications and is administered after removal of the first four litres (as described above). The risk is associated with the amount of fluid removed. Using the peritoneal catheter allows removal of smaller amounts of ascites (< 2 litres) and the risks of these complications are therefore negligible. To avoid electrolyte and protein depletion, patients in both interventions will be monitored with regular blood tests.

*Peritonitis*: Patients with diuretic resistant ascites have an increased risk of developing bacterial peritonitis. In addition, both interventions are associated with an increased risk of peritonitis. To reduce the risk of peritonitis, we will administer ciproxin prophylaxis to all patients.

*Bowel perforation*: Both interventions are associated with a potential risk of bowel perforation. The complication is very rare affecting less than one percent.

Risks associated with assessments of outcomes

The risks associated with blood sampling include local haematoma and pain.

The body composition will be assessed using dual-energy X-ray absorptiometry (DXA scan). The radiation associated with the scan corresponds to a conventional chest X-ray (0.02 mSv).

Potential Benefits

The potential benefits of the PleurX drainage system include improved management of ascites, quality-of-life, symptom management, and improved nutrition.

Primary Outcome Measure

- Paracentesis free survival

Secondary outcome measures

- Cumulative number of paracenteses
- Quality of Life
- Adverse events (as defined below under definition of adverse events and monitoring).

The assessment of outcome measures is described in Appendix A.

STUDY DESIGN

This trial will be conducted in compliance with the protocol, EN ISO 14155 ”Clinical investigation of medical devices for human subjects – Good clinical practice” and the applicable regulatory requirements.

Patient inclusion criteria

- Cirrhosis of any aetiology;

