- The PleurX Tunnelated Peritoneal Catheter is approved for permanent placement and catheter implantation is regular clinical practice prior to initiation of this study. Consequently the registration of medical device handling will include noting device LOT number in patient’s medical record and in the corresponding CRF.
- All peritoneal catheters are labeled with following information:
  - Manufacturers name and address: CareFusion, [name].
  - Exact description of package content.
  - Package content is STERILE.
  - LOT number.
  - Expiring date.
  - For single use only.
  - Warnings:
    - Do not use if package is damaged. Consult instructions for use. Contains phthalates.

Monitoring Procedures

Independent monitoring of the trial for clinical protocol and compliance will be conducted periodically (i.e., at a minimum of three monthly intervals) by qualified staff from the the GCP unit in the Capital Region. The sponsor-investigator will permit direct access to the study monitors and appropriate regulatory authorities to the study data and to the corresponding source data and documents to verify the accuracy of these data.

Other treatments

Other treatments that are considered necessary for the subject will be given at the discretion of the investigator. Administration of all other treatments will be recorded on the accompanying Case Report Form.

Procedures in case of emergencies

The investigator will ensure that the necessary procedures and expertise to handle emergency situations that may arise during the study will be available.

Adverse Events

Adverse events (AEs) are defined as any event, sign or symptom occuring during the study whether the AE is considered to be related to the intervention or not. All adverse events must be recorded in the patient's Case Report Forms.

If an AE occurs more than 1 week after the removal of the PleurX catheter or more than 1 week after completion of Visit 8, and there is no apparent causal connection or relation to the Pleurx catheter, this shall not be deemed to be an AE.

The median survival for patients with cirrhosis and diuretic resistant ascites is six months and mortality is therefore expected amongst study participants. Consequently fatal events due to chronic liver failure will not be categorised as a SADE.

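### The adverse-event list counts admissions for the allocated control treatment as AEs, and uses presumed non-relatedness to take liver-failure admissions out of the SAEs

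*Protocol*

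**What the plan says.** Under Secondary outcome measures the protocol lists "Adverse events (as defined below under definition of adverse events and monitoring". The Adverse Events section then sets a broad definition and a recording duty: "Adverse events (AEs) are defined as any event, sign or symptom occuring during the study", related or not, and "All adverse events must be recorded in the patient's Case Report Forms". Type, relationship, severity, start date and end date are required for each AE.

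Two exception lists follow.

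- **First list.** These events are said to have been judged by hepatologists "as not being associated with carrying a permanent tunnelated peritoneal catheter", and the consequence is stated as "As a result this list of events will not be categorised at SAE but will be registered as AE". The list includes "Hospitalisation du to large volume paracenthesis", changes in medication, planned outpatient visits for other chronic disease, and hospitalisations for chronic liver failure.
- **Second list.** Nine symptoms attributed to ascites, among them abdominal pain, nausea and dyspnoea, are collected by the quality-of-life questionnaire. "Therefore these side effects will not also be listed as Adverse Events".

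The SAE definition in the same section covers death, life-threatening illness, lasting harm, and hospitalisation or its prolongation. It has no relatedness condition. Relatedness enters only in the definitions of device effects (ADE and SADE).

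**The concern.** Large volume paracentesis is what the control arm is allocated to receive. The Interventions section describes it as done in hospital, with the patient staying until the fluid is drained. Registering each such hospitalisation as an AE turns delivery of the comparator into a recorded harm. The same procedure already drives paracentesis-free survival and the cumulative number of paracenteses, so it would enter the results a third time. Home drainage through the catheter generates no matching entry.

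The liver-failure rule is a different kind of fault. Whether an event is serious and whether it is related to the device are separate questions, and the protocol's definitions keep them separate. The list answers the first by means of the second. Both arms are affected, and the SAE table would leave out hospitalisations that the protocol's own definition includes.

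The stated objective covers harmful as well as beneficial effects, and patients and investigators are unblinded. The safety comparison therefore depends on clear classification rules.

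**Working it through.** The protocol states no figure for AE counts, so there is none to reproduce. The checks below give the size of the first problem and set the texts side by side for the other two.

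**1. AEs generated by the control treatment**

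Inputs:
- 16 patients per arm (Sample Size Considerations).
- Follow-up of 180 days (Visit 8).
- Paracentesis needed weekly, bimonthly or monthly (Ethical considerations). Bimonthly can mean twice a month or every two months.
- A two-week interval as a middle case. This is an assumption, suggested by the two-week re-accumulation criterion for eligibility, which is not a treatment schedule.
- Assumption: each paracentesis counts as one hospitalisation.

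Formula: AEs = 16 × 180 / interval in days.

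| Interval | Per patient | 16 controls, full follow-up |
|---|---|---|
| 7 days | 180/7 = 25.7 | 411 |
| 14 days | 180/14 = 12.9 | 206 |
| 30 days | 180/30 = 6 | 96 |
| 60 days | 180/60 = 3 | 48 |

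Allowance for deaths: the Background gives a median survival of about six months. Under exponential survival the mean time observed over six months is 6 × 0.5 / ln 2 = 4.33 months. The factor is 4.33/6 = 0.72, which gives about 297, 148, 69 and 35.

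**2. Effect on a comparison of patients with any AE**

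The protocol does not specify this analysis for AEs. It is an illustration, using the chi-square test at 5% that the Statistical analyses section names for group comparisons. Rejection probabilities come from exact binomial enumeration with 16 per arm. The true risk of any other AE is set equal in both arms, at 10% (the procedural risk under Potential Risks) or 59% (the upper end of the complication range in the Background). All controls are assumed to have at least one paracentesis hospitalisation. The share of PleurX patients with one is not stated, so it is varied from 0 to 70%.

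| Other-AE risk | PleurX share 0% | 50% | 70% |
|---|---|---|---|
| 10% | 1.00 | 0.97 | 0.66 |
| 59% | 0.94 | 0.42 | 0.12 |

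If 90% of controls are admitted, the 10% row becomes 1.00, 0.70 and 0.26. With paracentesis hospitalisations left out and a 10% risk in both arms, the rejection rate is 0.028. The distortion can thus be near-certain or modest. It shrinks as the background AE rate rises and as more PleurX patients need paracentesis.

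**3. Liver-failure hospitalisations**

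- SAE definition: hospitalisation is sufficient, and relatedness is not mentioned.
- List: hospitalisation for chronic liver failure is never an SAE, because it is deemed unrelated to the catheter.
- The same section handles deaths from chronic liver failure differently, exempting them only from the SADE category. That category does depend on relatedness.

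The first two statements cannot both be followed. Since these hospitalisations remain registered AEs, only SAE counts change.

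**4. Symptom exclusion**

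- Potential Risks: the risks of the peritoneal catheter and "large volume paracentesis include pain at insertion of the drain".
- Adverse Events: any sign or symptom is an AE, but nine symptoms of ascites, including abdominal pain, are not listed as AEs.
- Visit 1 and the grading section: procedure-related complications are collected at the procedure, and reactions are related to the allocated intervention and graded.

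The texts do not say which rule governs when a listed symptom follows a procedure.

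**The case against.** The best reply on the first point is that no pooled AE comparison is specified, that tabulation is commonly left to a statistical analysis plan, and that AE type is recorded, so paracentesis hospitalisations can be separated at analysis. That stands. A reader might infer that every AE count by arm is invalid, but the documents support this only for pooled totals and any-AE comparisons. PleurX patients who need paracentesis also add entries, and a paracentesis done as a day procedure might not be called a hospitalisation.

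On the liver-failure rule, the reference to evaluation by hepatologists could be read as case-by-case review. A fixed list makes classification in advance the likelier reading, and either way relatedness does not decide seriousness under the protocol's definition. Leaving a planned paracentesis admission out of the SAEs is not in itself a fault.

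On symptoms, the exclusion is framed around effects of ascites, and Visit 1, Visit 2 and the grading section provide a route for procedural reactions. A reader might infer that pain from the device would go unrecorded. The documents do not show that.

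A reader might also infer that all the rules favour PleurX. Only the paracentesis rule has a predictable direction. The other two apply to both arms, and their net effect depends on event rates that the protocol does not give.

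**Conclusion.** The point holds in limited form. Registering hospitalisation for the control treatment as an AE inflates any pooled AE total mainly in the control arm, by about 96 to 411 entries between monthly and weekly frequency with full follow-up (about 69 to 297 under the survival assumption). If bimonthly means every two months, the low end is 48, or 35 with deaths. These figures assume one hospitalisation per paracentesis.

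These counts should not be set against the 10% procedural risk times 16 patients. That would compare events with patients, and the 10% covers named procedural risks only, not all AEs.

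The liver-failure rule contradicts the SAE definition in its own section and makes SAE counts wrong by the protocol's own standard, in an unknown direction. The symptom exclusion is a lesser matter of unclear scope. The primary outcome is unaffected. The change should be made because an analysis plan can filter out paracentesis entries, but it cannot readily supply a seriousness classification that was never assigned.

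**What to change.** 1. Take planned paracentesis admissions, planned outpatient visits and medication changes as such off the AE list. Keep paracenteses in their own count, and record only their complications as AEs.
2. Classify hospitalisations for chronic liver failure as SAEs under the stated definition and report them by arm. Assess relatedness case by case, and confine any exemption to expedited reporting.
3. Add a sentence saying that the symptom exclusion does not cover listed symptoms, such as pain, that follow a procedure or lead to admission or catheter removal. This reconciles it with Potential Risks, the Visit 1 and Visit 2 procedures, the AE definition and the grading section.

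The cost is an amendment to the wording, revised CRF guidance and somewhat more SAE entries. No change to sample size, visits or the primary analysis is needed.
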